### 3.1 Proposed mechanisms of action:

DA neurons are damaged early in the PD disease process, which in turn causes activation of microglia. As the neurons degrade,  $\alpha$ -synuclein is released and taken up by the microglia, which in turn recruits circulating immune cells that infiltrate into the CNS, secrete proinflammatory cytokines, chemokines, and reactive oxygen species. These events eventually lead to a chronic inflammatory state and accelerated neuronal death through oxidative stress and apoptosis. Based on evidence from previous studies, we hypothesize that IV injection of MSC will help to reduce the neuroinflammatory response through the manipulation of microglia-mediated neuroinflammation.

The potential benefit of MSC therapy is hypothesized to rely on three specific actions. Paracrine immunomodulation and exosome-mediated activity play significant roles.

- Paracrine actions:

Paracrine factors as cell-derived microvesicles that perform intercellular communication. The release of trophic factors and immunosuppressant factors can enhance angiogenesis, inhibit fibrosis and apoptosis, and suppress free radical formation. The trophic factors stimulate the recruitment, retention, proliferation, and differentiation of tissue-residing stem cells, and produce an extracellular matrix that supports neural cell attachment, growth, and axonal extension. Together all these actions can create a favorable environment for regeneration and allow for an intrinsic restorative process to occur.

MSCs can secrete numerous growth factors and cytokines, including the following: Brain-derived neurotrophic factor (BDNF), nerve growth factor (NGF), glial cell-derived neurotrophic factor (GDNF), fibroblast growth factors 2 and 8 (FGF2 and FGF8), ciliary neurotrophic factor (CNTF), neurotrophin-3 (NT-3), hepatocyte growth factor (HGF), platelet-derived growth factor (PDGF), vascular endothelial growth factor (VEGF), insulin-like growth factor 1 (IGF-

1) and stromal cell-derived factor-1 (SDF-1). GDNF, BDNF, FGF, and CNTF have been shown to elicit neurotrophic and neuroprotective effects on DA neurons. These neuro-regulatory molecules promote neuronal survival and regeneration, as well as endothelial cell proliferation and angiogenesis.

MSCs also activate microglia and astrocytes. Activated microglia produce trophic factors that stimulate DA neural regeneration and provide signals that promote endogenous neural stem cells and glial differentiation. MSCs have been shown to suppress or activate immune responses; through cell-cell contact and release of different factors, they evoke a cellular immune response by expressing immunomodulatory mediators such as indoleamine 2,3-dioxygenase (IDO) and induced nitric oxide synthase (iNOS). On the other hand, MSC secretion of the anti-inflammatory cytokines TGFβ, IL-1ra, IL-10, and subsequent down-regulation of IL-2 and IL-15 may suppress the activities of macrophages, neutrophils, T and B lymphocytes, dendritic cells and natural killer cells.

- Exosomes:

MSC secrete extracellular vesicles known as exosomes derived from the endosomal membrane. Exosomes carry nucleic acids, lipids, and proteins, including micro RNAs; they elicit diverse cellular responses and can function as an intercellular communication vehicle for modulation of cellular processes. Exosomes support the maintenance of immune homeostasis within the tissue and allow for a dynamic response to the external tissue microenvironment. They potentially restore tissue function by providing catalytically active enzymes to promote homeostasis.

### 3.2 Advantages

MSC possess several advantages over other stem cell therapies that make them an attractive therapeutic for neurodegenerative disorders:

- Easily procured and expanded on a large scale.
- Little to no ethical issues or controversies.
- Able to differentiate along several lineage pathways.
- Capable of migrating to sites of injury, including crossing the brain-blood barrier.
- Immunomodulatory and anti-inflammatory properties.
- Low probability of being tumorigenic.
- Amenable to genetic modification.

### 3.3 MSC Pharmacology

#### Absorption and Distribution:

Animal studies have shown that following intravenous administration, the majority of allogeneic MSCs are trapped in the lungs upon the first passage and can remain there for up to approximately a week. Under inflammatory conditions, MSC may persist at distal sites of injury up to 5-8 days post-injection . In rat models of PD, xenogeneic MSC injected I.V. were detected in brain tissue between 2-7 days post-administration .

#### Metabolism and Excretion:

Allogeneic MSC migrate to the spleen and the liver within 2-5 days post-injection and are presumably phagocytized by local macrophages at these sites within 14 days .

#### Toxicology:

Up to  $2 \times 10^6$  cells/mouse have been injected (equivalent to  $1 \times 10^{11}$  cells/kg) with no serious adverse effects . The development of an immune response directed against allogeneic MSC has been reported in several different animal models; thus far, the only measurable consequence appears to be decreased survival and engraftment of the injected cells .

### **3.4 Pre-clinical and clinical experience of MSC in PD and other disorders**

There is substantial evidence from animal models and from chronic human diseases that MSC transplantation by intravenous administration can restore immune system homeostasis and stimulate DA regeneration, thus having the potential to slow the progression of PD.

#### Animal Models

Several studies using animal models of PD have found that intravenous (I.V.) or intra-arterial administration of MSC can protect dopaminergic neurons and may improve motor function. Table 1 provides a list of animal studies that assess the effect of intravenous MSC, which includes: 6-OHDA, Preformed fibril model + MPTP, MPTP + 3-NP, MPTP, and a transgenic MSA model. Most of the studies showed dopaminergic survival (increased TH+ neurons), reduced inflammatory cytokines, decreased microglial activation, and some behavioral improvement. Intriguingly, some of these models suggest that the therapeutic effects of intravenous delivery of MSCs may not even be dependent on the status of the BBB because of the profound impact of MSCs on the peripheral immune responses. Our group's recent meta-analysis of 25 studies of MSC therapy in animal models showed safety and efficacy. The meta-analysis demonstrated that the I.V. route of administration had a more substantial effect on limb function as well as improved rotational behavior.

## Clinical Experience in Neurodegenerative disease

**Table 1. Animal Models**

| Model                            | Cell type                                            | # cells/kg                                 | Injection site                                  | Follow-up             | Results                                                                                            | Ref            |
|----------------------------------|------------------------------------------------------|--------------------------------------------|-------------------------------------------------|-----------------------|----------------------------------------------------------------------------------------------------|----------------|
| 6-OHDA rat                       | MSC transfected with CDNF                            | 2 x 10                         | Intrastriatal, intraventricular or jugular vein | 6 weeks               | Behavioral improvement (better for intrastriatal) and Increased TH+ neurons                        |  |
| 6-OHDA rat                       | Human adipose derived MSC                            | ?                                          | Intraventricular into SN                        | 3 days                | Evidence of S100 positive BDNF cells and endothelial cells derived from MSC                        |   |
| 6-OHDA rat                       | Human BM-MSC (up to 6 th passage)         | 1 x 10                         | Femoral vein                                    | 26 or 80 days         | Increased TH+ neurons
Behavior improved out to 80 days. No evidence of hMSC engraftment         |   |
| 6-OHDA rat                       | Rat BM-MSC GFP transfected (2 nd passage) | 1 x 10                         | Femoral vein                                    | 2d. 1wk.
4 wks     | Cells in lung and brain at 2 days, also at 1 week                                                  |   |
| MPTP mouse and a-syn-inoculation | Human MSCs (2 nd passage)                 | 1 x 10                         | Tail Vein                                       | 7 days                | Reduced levels of immunoreactivity for both a-synuclein and ThT                                    |  |
| (PLP)- αSYN mouse (MSA)          | GFP positive syngeneic MSC                           | 5 x 10                         | Tail Vein                                       | 4 weeks               | No behavior improvement
Reduced inflammatory cytokines in the brain                             |  |
| MPTP and 3-NP (MSA)              | Human BM-MSC (6 th passage)               | 1 x 10                         | Tail Vein                                       | 4 weeks               | Increased TH+ Nuer-N+ cell survival
Decreased microglial activation                             |   |
| MPTP mouse                       | Human BM-derived MSC (6 th passage)       | 1 x 10                         | Tail Vein                                       | 2-4 weeks             | Reduced α-syn in the brain, increased autophagolysosomes in DA neurons                             |   |
| MPTP rat                         | BMMC or BM-MSC (4 th passage)             | 5 x 10 
1 x 10  | Jugular vein                                    | 1-8 days              | No behavioral improvement
MSC injected had slightly better neuron survival                      |   |
| MPTP mouse                       | Mouse BM-derived MSC                                 | 1 x 10                         | Tail Vein                                       | 3, 7, 14, and 28 days | Recovery of BBB integrity, suppression of microglial activation and Increased TH+ neurons survival |  |

Venkataramana *et al.* in an open-label Phase I study demonstrated the safety of autologous MSC transplantation into sublateral ventricular zone of 7 PD patients, reporting a decrease by 18% of the conventional “off” Unified Parkinson’s disease Rating Scale (UPDRS) -Total score after one year and 26% following 2 years post-treatment. There was a substantial reduction in total levodopa dosing for the PD patients with no adverse effects reported. The same group reported results from a 2 year pilot clinical study demonstrating feasibility, safety, and efficacy of bilateral transplantation of allogeneic MSCs in 8 PD patients with a mean improvement of 31% in the off UPDRS-Total score. Neither of these studies reported any serious adverse events related to treatment .

To date, there have been studies of the effects of MSC therapy on three neurodegenerative diseases, including multiple system atrophy (MSA), multiple sclerosis (MS) and amyotrophic lateral sclerosis (ALS):

- Dongmei *et al.* showed that intrathecal injection of umbilical cord mesenchymal stem cells (UC-MSC) is safe and can delay the progression of neurologic deficits in MSA-C patients. They reported 3 symptoms as side effects after intrathecal injection, including dizziness, back pain, and headache that disappeared between 1-3 days, and were attributed to the lumbar puncture procedure. Xi *et al.* tried a comprehensive cell-based neurorestorative therapy (I.V. UC-MSC, intrathecal Schwann cells, and transplantation of olfactory ensheathing cells) for patients with multiple system atrophy, in which they proved safety and to some extent benefit with improvement in total Unified Multiple System Atrophy Rating Scale (UMSARS). Lee *et al.* evaluated the feasibility of consecutive intra-arterial and intravenous MSC treatment for MSA patients and proved safety and a significant improvement on the UMSARS.
- Karusis *et al.* showed that one intrathecal and one intravenous administration of MSCs in patients with MS and with ALS is clinically feasible, relatively safe, and induces immediate immunomodulatory effects. Connick *et al.* performed an open-label Phase 2a proof-of-concept study and concluded that autologous MSCs were safely given in one I.V. dosage for secondary progressive MS. There was evidence of structural, functional, and physiological improvement after treatment. Liang *et al.* used allogeneic MSC transplantations for the treatment of multiple sclerosis resulting in disease stabilization and improved quality of life in a single MS patient. Hou *et al.* showed that I.V. and intrathecal administration of umbilical cord and bone marrow-derived MSCs over 4 years in a patient with relapsing-remitting multiple sclerosis was safe and effective.
- Mazzini *et al.* showed safety of MSC transplantation in the dorsal spinal cord in patients with amyotrophic lateral sclerosis. Additionally, Navabi *et al.* have also shown that intravenous (IV) and intrathecal (IT) transplantation of BM-derived stromal cells is safe and feasible in patients with amyotrophic lateral sclerosis.

### Clinical Experience in other diseases

Allogeneic MSC have been used worldwide in research for the past decade, available data indexed in PubMed contains results for a wide range of diseases including acute graft-versus-host disease (aGVHD), ankylosing spondylitis, systemic lupus erythematosus (SLE), Crohn's disease, human immunodeficiency virus (HIV), ulcerative colitis, psoriasis, leukemia, diabetes mellitus (DM), chronic obstructive pulmonary disease (COPD), interstitial lung disease (ILD), asthma, partial medial meniscectomy, orthogenesis imperfecta, spinal cord injuries, ischemic cardiomyopathy, myocardial infarction, heart failure, critical limb ischemia (CLI) and cerebral palsy.

Currently, there are 84 allogeneic mesenchymal stem cell trials registered in the U.S. National Institutes of Health (NIH) database conducted by investigators in the USA, Australia, Belgium, China, Denmark, Greece, Germany, India, Iran, Japan, Korea, Malaysia, Spain, and Vietnam.

## Dosage, Intervals, and Route of Administration for allogeneic MSC

Different delivery routes for MSC have been tested, including intra-arterial, I.V., intra-articular, intrathecal, intramuscular, transendocardial, and intra-bone marrow. An I.V. infusion is the least invasive and therefore the safest. Available literature reported eleven studies performed in the USA, Australia, Japan and China that used I.V. infusion as a delivery route; none of them had a serious adverse event (SAE) related to I.V. infusion of MSC and none had specific reactions following serial infusions. Dosages of I.V. infusion used in the studies mentioned above ranged from  $1-150 \times 10^6$  MSC/ kg, with each of the doses proven to be safe and showing some degree of efficacy. Eight of the eleven trials included serial infusions ranging from 2 to a maximum of 12 dosages, scheduled as often as twice a week or as far apart as once every 6 months. Serial infusions are an important consideration in PD since our data show that PD is a chronic neuroinflammatory condition that is relentlessly progressive and unlike an acute injury, requires serial infusions to modify and maintain the immune system response.

### **3.5 Safety and Tolerability**

Monitoring for safety after administration of undifferentiated MSC focus on acute hypersensitivity reaction and a sub-acute or delayed antibody-mediated reaction that can occur within 3-4 weeks of the infusion. A primary concern, although extremely rare, in MSC infusion therapy is the development of a hypersensitivity reaction. Transient (lasting several hours) fever is the most common but again rare administration side effect. An acute, more serious hypersensitivity reaction causing fever, confusion, kidney, liver, or other organ damage, hemolytic anemia or pneumonitis has a very low risk of occurrence. Additionally, the systemic or intravenous route of administration means that the MSC can be distributed to many different tissues and organs in the body and we know that most will end up in pulmonary tissue and that the small molecules will distribute throughout the circulation.

The immune privileged status of MSC has been demonstrated using expanded undifferentiated and differentiated MSC *in vitro* culture. The cell surface of these cells expresses intermediate levels of human leukocyte antigen (HLA) major histocompatibility complex (MHC) class I molecules and negligible levels of HLA class II and Fas ligand. There is no expression of the co-stimulatory molecules B7-1, B7-2, CD40 or CD40L, and when exposed to allogeneic lymphocytes, they fail to elicit a reactive response. However, with alloantibody production following repeated doses of MSC, no life-threatening host vs. graft responses have been reported.

Lalu *et al* reviewed the safety of systemic MSC administration in humans in a meta-analysis of 36 studies. Based on these analyses, MSC therapy appears safe with transient fever as the only significant administration side effect.

To prove the safety and feasibility of the use of intravenously deliver allogeneic bone marrow-derived MSCs in patients with PD, our group designed and conducted the first USA single-center open-label dose-escalation phase 1 study and we demonstrated that a single infusion of allogeneic

MSCs is safe and well-tolerated in mild to moderate PD patients. The treatment effect likely relies on peripheral immune modulation. The study recruited 20 subjects with mild-moderate PD that were sequentially assigned to one of four doses: 1, 3, 6, or 10 X 10^6 MSCs/kg given IV and evaluated at 3, 12, 24, and 52 weeks post-infusion. Primary outcome safety measures were defined as the absence of immediate transfusion reaction, study-related adverse events, organ damage, or immunogenic reactions. Secondary outcomes were defined by the therapy's impact on peripheral markers, PD progression, and changes in brain perfusion.

All 20 patients received a single MSCs IV infusion. During the first 24 hrs post-infusion, three patients reported TEAEs, one with phlebitis, one with an antecubital fossa hematoma, and one with a headache (*Table 2*). The first patient had 3 cm superficial phlebitis Grade 2 Infusion-Related Allergic Reactions (NCI-CTCAE criteria) that required local medical management. The other two patients had mild symptoms and did not require any treatment. All patients left the research unit with full resolution of their symptoms. In subsequent follow-up, 50% of the patients reported TEAEs; most of them were mild, with dyskinesia (20%, N=4) and hypertension (20%, N=4) as the most common. Two of the patients experiencing dyskinesias required levodopa reduction for resolution and the remaining resolved without intervention. All hypertension cases were reported between 3 and 12 weeks after infusion and were followed by their primary care physicians. Of those, three cases were transient, and one patient was diagnosed with stage 2 hypertension and is currently under medical management.

There was no response to donor HLA over the 12-month study. At 52 weeks CCL2 declined by 15% ( $p<0.01$ ), and CCL22 by 29% ( $p<0.05$ ), along with an increase in BDNF 46% ( $p<0.05$ ). The highest dose had the most significant effect on reducing OFF UPDRS motor -14.4 ( $p<0.01$ ) and total scores (-20.8,  $p<0.001$ ). Further, there was an increase in basal ganglia perfusion at 24 weeks ( $p<0.001$ ).

| Body System      | Adverse Reaction          | Group A
N=5
(100%) | Group B
N=5
(100%) | Group C
N=5
(100%) | Group D
N=5
(100%) | AE Relationship to MSC |
|------------------|---------------------------|--------------------------|--------------------------|--------------------------|--------------------------|------------------------|
| Cardiovascular   | Hypertension              | 2 (40%)                  | 2 (40%)                  | 0                        | 0                        | Unlikely related       |
|                  | Phlebitis b    | 0                        | 0                        | 0                        | 1 (20%)                  | Related                |
|                  | Hematoma b     | 0                        | 0                        | 1 (20%)                  | 0                        | Related                |
| Gastrointestinal | Nausea a       | 1 (20%)                  | 2 (40%)                  | 0                        | 0                        | Possibly related       |
| Neurologic       | Headache b     | 0                        | 1 (20%)                  | 0                        | 0                        | Possibly related       |
|                  | Dyskinesia                | 1 (20%)                  | 0                        | 2 (40%)                  | 1 (20%)                  | Probably related       |
| Hematology       | CLL                       | 0                        | 0                        | 1 (20%)                  | 0                        | Possibly related       |
| Lab              | ↓Lymphocytes a | 3 (60%)                  | 2 (40%)                  | 0                        | 1 (20%)                  | Possibly related       |
|                  | ↑Basophils a   | 1 (20%)                  | 1 (20%)                  | 1 (20%)                  | 1 (20%)                  | Possibly related       |

Data shows n and (%) per dose group. CLL, Chronic Lymphocytic Leukemia. a: Mild and transient. bThere were three AEs related to the infusion procedure (phlebitis, antecubital fossa hematoma, and headache). The remaining AEs were reported at follow-up and 3 patients required management, one for hypertension and two for dyskinesias.

#### 4. Design

Phase IIa double-blind, randomized controlled clinical trial of allogeneic bone marrow-derived mesenchymal stem cells as a disease-modifying therapy for PD. Forty-five men and women between 50 and 79 years of age who meet the UK Brain Bank criteria for idiopathic PD and who have a Hoehn and Yahr of <3 in the OFF medicine state and are between 3-10 years from the onset of disease diagnosis will be recruited to participate. Subjects will be randomized 1:1:1 to 1 of the

3 following groups: 2 infusions of  $10 \times 10^6$  MSC/Kg every 4 months and one placebo infusion; 3 infusions of  $10 \times 10^6$  MSC/Kg every 4 months and 3 infusions of placebo every 4 months. *Figure 1.* The subjects will be followed for a total of 88 weeks.

[figure not shown]

## 5. Study objective and outcomes

The primary objective of this study is to select the safest and most effective number of repeat doses of allogeneic bone marrow-derived mesenchymal stem cell infusions to slow the progression of PD.

### 5.1 Outcomes

#### 5.1.1 Primary outcome

The primary goal of this trial is to select the safest and most effective number of repeat doses of allogeneic bone marrow-derived MSC with the aim to slow the progression of PD as determined by the change on the motor section of the MDS-UPDRS ( $\geq -5$ ) in each active treatment arm versus placebo between screening and 62 weeks follow-up.

#### 5.1.2 Secondary outcomes

Assess 1) safety and tolerability; 2) secondary measurements of clinical efficacy and 3) explore putative mechanisms of action for the effect of MSC

1. MSC therapy will demonstrate safety and tolerability comparable to placebo in terms of serious adverse reactions and immunologic responses.

- New-onset organ failure defined as a significant acute change in the kidney or liver function, leukocytosis, leukopenia or anemia sustained over 3 months; > 75 % reduction in GFR compared to baseline; altered liver function as defined by ALT >150 U/L and or total bilirubin >1.6 mg/dl; or leukopenia defined as < 4K WBC count or anemia as defined by Hgb < 12 for men and < 11 for women.
  - Immunologic responses: Donor specific antibodies (DSA) in serum of patients will be measured and compared to baseline to determine if there is a development of antibody response to donor HLA. (Please refer to section 11.2)
2. MSC therapy will improve motor function, disability, quality of life, non-motor symptoms, cognition, and behavioral changes relative to placebo.
- Motor function: characterized by a change in MDS-UPDRS Total and Motor scores and Timed-Up-and-Go (TUG) from baseline. Immediate response will be assessed at weeks 29, 39, 52, and 78. Normal progression in UPDRS-T is defined by > 8-14 points per year Therefore abnormal clinical deterioration is an increase of >12 points per year in the “Off” state. For the UPDRS-M, the literature supports a natural progression of 3-6 points per year and this equivalent for the MDS-UPDRS motor section; therefore, abnormal clinical deterioration is an increase of > 6 points per year. TUG progression is defined as a +/- 3 seconds difference every 6 months.
  - Global measurement of disability as measured by the change in the screening “Off” modified Hoehn and Yahr (H&Y) at the final visit. Expected progression is defined as a < 1.0 increase in H&Y every 2 years. Therefore, clinically significant deterioration would be > 0.5 increase in the H&Y over 1-year.
  - Quality of life: based on changes in the modified Schwab and England activities of daily living scale (ADL), Parkinson's Disease Questionnaire 39 (PDQ-39) and EuroQol- 5 Dimension (EQ-5D) from screening and at the final visit. The normal progression is an annual change of 10% in ADL and a change of less than 10% of the PDQ-39 at the final visit compared with the screening visit. Therefore a change of > 10% in ADL or the PDQ-39 over the 1 year study period will be considered clinically significant. For the EuroQol- 5 Dimension (EQ-5D), simulation-based estimates defined the minimally important difference (MID) index score to be between 0.037 and 0.069.
  - Non-motor symptoms: The non-motor symptoms questionnaire (NMS) and The University of Pennsylvania Smell Identification Test (UPSIT- 40 odor test booklet).
  - Cognitive function: measured by the change in Montreal Cognitive Assessment (MoCA) from screening to final visit. Normal change is less than 3 points per year. Therefore a  $\geq 3$  point change over a one year study will be considered clinically significant.
  - Behavioral changes: The Columbia Suicide Severity Rating Scale (C-SSRS), Geriatric Depression Scale-Short Form (GDS-SF), and Parkinson Anxiety Scale (PAS). Suicidal ideation will be assessed by the Columbia Suicide Severity Rating Scale (C-SSRS); any

positive response to any of the questions will be considered significant and would require further investigation. A score of 8 or more in the Geriatric Depression Scale will be considered significant and would require further investigation.

3. Explore putative mechanisms of action for the effect of MSC therapy. We will assess the putative paracrine mechanism of MSCs using neuroimaging and measuring concentrations of cytokines, chemokines, growth factors, neurotransmitters and alpha-synuclein oligomers in the blood (serum or plasma) and CSF.
  - Neuroimaging: 3 imaging time points per patient, baseline, week 40, and week 88.
    - Perfusion MRI: We will measure resting cerebral blood flow (CBF) using a pseudo-continuous arterial spin labeling (pCASL) MRI sequence with gradient-echo echo-planar imaging (EPI). Recent ASL studies of PD patients report wide-spread cortical hypoperfusion and, subcortically, hypoperfusion of the caudate nucleus.
    - Diffusion-weighted MRI (for DTI analysis): will be used to examine white matter microstructures, which represent the structural pathways linking specific cortical and subcortical regions. Specifically, we expect to find increased fractional anisotropy and decreased mean diffusivity along white matter fibers that link regions exhibiting increased functional connectivity such as substantia nigra and dorsal striatum.
    - Neuromelanin MRI: neuromelanin-sensitive and iron-sensitive MRI sequences can robustly detect and quantify the neuromelanin loss, and iron accumulation in the substantia nigra pars compacta (SNc) and locus coeruleus (LC). We expect no changes in the neuromelanin (NM) signal in the SNc at 40 weeks.
  - Peripheral responses: serum or plasma concentrations of cytokines, chemokines, growth factors, and neurotransmitters will be measured at each follow-up and compared to baseline. Preliminary data generated in our laboratory demonstrated that MSCs effect likely relies on peripheral immune modulation, promoting an anti-inflammatory state.
  - Alpha-synuclein oligomers: Total and phosphorylated alpha-synuclein in plasma will be measured using ELISA and total alpha-synuclein in CSF will be measured using Protein Misfolding Cyclic Amplification (PMCA). Kinetic parameters seem to correlate with disease severity measured by H&Y.

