### 8.5.3 TUG (Timed Up and Go Test)

Time in seconds required to stand from a chair, walk 7m, turn, walk back to the chair and sit down. The principal investigator will conduct the assessment at each clinical visit.

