### 8.5.4 ADL (Modified Schwab and England Activities of daily living score)

The Schwab & England scale is a physician assessment of the subject's level of independence. The subject will be scored on a percentage scale reflective of his/her ability to perform acts of daily living in relation to what he/she did before Parkinson's disease appeared. Scores range from 0% to 100% in increments of 10%, where 100% is completely independent and 0% is only vegetative functions. The principal investigator will conduct the assessment at each clinical visit (See Appendix F for a copy of the ADL).

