## 14.3 Statistical analysis

Hypothesis 1.1. At least one active MSC group will demonstrate improved scores ( $\geq -5$ ) relative to placebo at 62 weeks follow-up. Generalized linear modeling will evaluate the MDS-UPDRS motor section as a function of treatment. Application of the decision-rules, discussed in the Sample Size Section, to the resulting posteriors will identify the candidate doses that warrant further investigation.

Hypothesis 2.1. Generalized linear modeling will characterize serious adverse reactions, significant worsening of general and motor functional state, activities of daily living, and peripheral immunologic responses. In each case, the subtraction of the posterior distribution for the treatment condition from the posterior distribution of the placebo condition will permit estimates of the posterior probability that the active condition is better than or equal to the control.

Hypothesis 2.2. Generalized linear modeling will estimate the improvement in motor function, disability, quality of life, non-motor symptoms, cognitive and behavioral symptoms as a function of treatment.

Hypothesis 3.1. Bayesian, multilevel structural equation modeling will evaluate the degree to which cytokines, chemokines, growth factors, and neurotransmitters transmit the effect of treatment to the MDS-UPDRS motor section at 62 weeks.

Hypothesis 3.2. Separate multilevel generalized linear modeling to account for correlations due to repeated observations within participants will evaluate the MDS-UPDRS motor section as a function of time and time-varying covariates, including kinetic parameters of  $\alpha$ Syn-PMCA in plasma and CSF before and after treatment.

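### Section 5.1.2 defines TUG progression in both directions, so a patient who becomes 3 seconds faster is classed as progressed

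*Protocol*

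**What the plan says.** Section 5.1.2, in the motor function item of the secondary outcomes, states: "TUG progression is defined as a +/- 3 seconds difference every 6 months". Section 8.5.3 defines the test as "Time in seconds required to stand from a chair, walk 7m, turn, walk back to the chair and sit down", so a longer time is a worse result.

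The neighbouring limits in section 5.1.2 carry a direction. For the motor UPDRS: "therefore, abnormal clinical deterioration is an increase of > 6 points per year". For Hoehn and Yahr: "Therefore, clinically significant deterioration would be > 0.5 increase in the H&Y over 1-year".

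Three other limits in section 5.1.2 have no sign but are worded differently from TUG. For ADL and PDQ-39: "Therefore a change of > 10% in ADL or the PDQ-39 over the 1 year study period will be considered clinically significant". For MoCA, a 3-or-more "point change over a one year study will be considered clinically significant". None of the three calls the change progression.

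On analysis, Hypothesis 2.1 in section 14.3, repeated for the interim analysis in section 14.4, models "significant worsening of general and motor functional state, activities of daily living", among other items. Hypothesis 2.2 models improvement in motor function and the other clinical domains by generalized linear modelling. Neither cites a cut-off from section 5.1.2.

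**The concern.** The TUG sentence attaches the word progression to a difference of either sign. Because the scale has a known bad direction, half of the definition describes benefit. This is something the protocol states wrongly, not a detail left to a statistical analysis plan.

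The stake is any categorical use of the definition. Section 5.1.2 expects MSC therapy to improve motor function relative to placebo. A progression category that also collects improvers works against showing that: as an active arm shifts towards faster times, it loses worseners from the category but gains improvers. The obvious place for such use is the worsening analysis under Hypothesis 2.1, since TUG is listed under motor function.

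**Working it through.** **Step 1: direction of scale against direction of rule**

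| Measure | Worse means | Rule in 5.1.2 | Term used |
|---|---|---|---|
| Motor UPDRS | higher score | increase of more than 6 points per year | deterioration |
| Hoehn and Yahr | higher stage | increase of more than 0.5 over 1 year | deterioration |
| TUG | longer time | plus or minus 3 s per 6 months | progression |

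Of these three, only TUG labels a move in the good direction as getting worse.

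**Step 2: is there a plan figure to reproduce?** No. The protocol gives no SD, expected mean or event rate for TUG change. The 72% in section 14.2 belongs to the primary MDS-UPDRS motor rule and does not enter here.

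**Step 3: size, on assumed values.** Let the 6-month TUG change be normal with mean m (positive is slower) and SD s. Both are assumptions, as is reading the rule as an absolute change of at least 3 s.

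- Worsening part: W = 1 − Φ((3 − m)/s)
- Improving part: I = Φ((−3 − m)/s)
- Literal rule: W + I. Worsening-only rule: W.

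At s = 3:

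- m = +1: W = 1 − Φ(0.667) = 0.252; I = Φ(−1.333) = 0.091; sum 0.344 (from unrounded values)
- m = 0: W = 1 − Φ(1) = 0.159; I = 0.159; sum 0.317
- m = −1: W = 1 − Φ(1.333) = 0.091; I = Φ(−0.667) = 0.252; sum 0.344

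The literal rule gives the same 34.4% for a mean worsening of 1 s and a mean improvement of 1 s. Improvers make up 0.091/0.344, about 27%, of those flagged in the first case, 50% when the mean change is zero, and 73% in the last.

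**Step 4: two treatment scenarios, each a 1 s benefit, at s = 3**

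- Placebo +1 s, active 0 s: literal 34.4% versus 31.7% (gap 2.7 points); worsening-only 25.2% versus 15.9% (gap 9.3 points). The benefit is diluted.
- Placebo 0 s, active −1 s: literal 31.7% versus 34.4%; worsening-only 15.9% versus 9.1% (gap 6.8 points). The benefit is reversed in sign.

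At 15 per arm (section 6.5), 2.7 points is 0.027 × 15 = 0.4 of a patient and 9.3 points is 0.093 × 15 = 1.4 patients.

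**Step 5: range over the assumed SD (percent meeting the rule)**

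| SD (s) | Literal, m = 0 | Literal, m = +1 or −1 | Worsening-only, m = +1 | Worsening-only, m = 0 | Worsening-only, m = −1 |
|---|---|---|---|---|---|
| 2 | 13.4 | 18.1 | 15.9 | 6.7 | 2.3 |
| 3 | 31.7 | 34.4 | 25.2 | 15.9 | 9.1 |
| 4 | 45.3 | 46.7 | 30.9 | 22.7 | 15.9 |
| 5 | 54.9 | 55.6 | 34.5 | 27.4 | 21.2 |

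At every SD shown, the first scenario is diluted and the second reversed. The literal gap shrinks from 4.7 points at SD 2 to 0.7 at SD 5. The worsening-only gap stays between 7.1 and 9.3 points in the first scenario and between 4.4 and 6.8 in the second.

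**The case against.** The strongest reply is that no planned analysis is shown to use the definition. Section 5.1.2 characterizes motor function by change from baseline, TUG included, and Hypothesis 2.2 models improvement directly. Hypothesis 2.1 already says worsening, which supplies a direction, and cites no limit. The only place that puts numbers on a significant worsening of functional motor state is the list of mandatory DSMB reviews in section 16, which uses MDS-UPDRS and Hoehn and Yahr, not TUG. All of this stands. It makes the consequence conditional and the point a small one, but it does not make the TUG sentence correct. If the plus-or-minus sign was meant as roughly 3 seconds, the sentence has neither a direction nor a firm threshold and still needs rewording.

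A reader might infer that the protocol counts improvers together with worseners. It does not say so; no progression count is prescribed on TUG or on the other scales.

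A reader might also extend the error to ADL, PDQ-39 and MoCA. The text does not support that. Those changes are called clinically significant, and a limit for meaningful change can apply in either direction. For ADL and PDQ-39 the preceding sentence, on normal progression, points to worsening. The scale directions are given in sections 8.5.4, 8.5.5 and 8.5.7, and nothing pools the two directions.

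Finally, a reader might conclude that the rule turns benefit into harm. That happens only when placebo does not drift. The protocol describes Parkinson's disease as progressive and aims to slow it, so a worsening placebo arm is at least as natural an assumption; there the benefit is diluted, not reversed.

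**Conclusion.** The point holds for TUG. As written, the definition classes a patient who is 3 seconds faster as progressed, against the test's own scale and unlike the UPDRS and Hoehn and Yahr rules beside it. The text alone settles this; no assumption is needed.

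The size rests on assumptions: a categorical use that the protocol does not specify, normally distributed change, an SD that the protocol does not give, and an assumed placebo drift. At SD 3 s, a 1 s benefit appears as 34% versus 32% instead of 25% versus 16% if placebo worsens by 1 s, and as 32% versus 34% instead of 16% versus 9% if placebo is stable.

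This is a minor defect in one secondary-outcome definition. The unsigned ADL, PDQ-39 and MoCA limits are not errors. The primary outcome, its decision rule, the sample size and the DSMB triggers are unaffected.

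**What to change.** In section 5.1.2, replace the TUG sentence with one that defines progression as an increase in TUG time of 3 seconds or more per 6 months, and adds that a decrease of 3 seconds or more is reported separately as improvement. Keep the numerical limit.

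Optionally, in the same edit, state which direction is worsening for the other limits: a decrease for ADL and MoCA, an increase for PDQ-39. This is a clarification only.

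The cost is wording. No visit, assessment, sample size or model changes.
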